### Sample size

A prospective sample size calculation has estimated that 306 participants (i.e. approximately 153 participants per group) are required to provide 80 % power to detect a clinically worthwhile difference of a 50 % reduction in injury in the intervention group (alpha set at 5 %). The sample size for the study was calculated assuming: (i) a combined incidence of injury of 30 % for medial tibial stress syndrome, patellofemoral pain, Achilles tendinopathy, and plantar fasciitis/plantar heel pain, and (ii) a drop-out of 20 %. The estimated incidence of lower limb injury was based on published data from studies investigating injury among Defence members completing basic training [2, 23, 24]. The drop-out rate for this trial was conservatively selected at the higher end of previous trials investigating the use of foot orthoses for the prevention of injuries in defence settings [25, 26], while also taking into account the completion rate of naval recruits undertaking the 11 weeks of basic training at HMAS Cerberus in the previous 12 months.

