### Outcome measures

The *primary outcome measure* will be the combined incidence of the four common lower limb injuries (medial tibial stress syndrome, patellofemoral pain, Achilles tendinopathy, and plantar fasciitis/plantar heel pain) as determined at medical appointments and by assessors at the exit interview (week 11).

*Secondary outcomes* include:(i)the overall incidence of lower limb pain as determined by pain drawings in self-report diaries, measured at week 11;(ii)the severity (usual and worst) of over-use lower limb pain as determined by the 100 mm VAS in self-report diaries, measured at week 11;(iii)the time (in days) to lower limb injury and pain as determined by self-report diaries and navy medical records, measured at weeks 1 to 11;(iv)time to drop-out from injury (in days) as determined by navy administration records, measured at weeks 1 to 11;(v)the type, frequency and severity (mild, moderate or severe) of self-reported adverse events (such as new pains, shoe/insole discomfort and blisters) will be obtained from the self-report diaries, measured at weeks 1 to 11;(vi)lost training days as determined by navy administration and medical records, measured at weeks 1 to 11;(vii)shoe comfort will be measured using a 100 mm visual analogue scale, measured at baseline and week 11;(viii)general health status will be determined using the Short-Form-12 (SF-12) Version 2 questionnaire [31], measured at baseline and week 11.

Shoe comfort will be determined using a 100 mm visual analogue scale, which has been shown to have good reliability [39]. The left end of the scale (0 mm) is labelled “not comfortable at all” and the right end of the scale (100 mm) is labelled “most comfortable imaginable”. Participants will be instructed to place a mark on the scale that represents their perceived comfort rating. Similarly, pain will be determined using a 100 mm visual analogue scale. To indicate the range of pain to participants, the left end of the scale (0 mm) is labelled “no pain” and the right end of the scale (100 mm) is labelled “worst pain imaginable”. The VAS has been shown to be a valid [40] and reliable [39] measure of pain.

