### Statistical analysis

Statistical analysis will be performed using SPSS version 22.0 or later (SPSS Corp, Chicago, Ill, USA) using the intention-to-treat principle, where all randomised participants will be included in the final analyses. The endpoint will be the completion of the 11 weeks of basic training for each participant. Multiple imputation will be used to replace any missing data using five iterations, with age, and group allocation as predictors [43]. The exception will be for the variable adverse events where no data substitution will be applied.

Participant characteristics and baseline data will be summarised by descriptive statistics. Distribution of continuous variables will be checked for normality and transformation will be carried out if necessary prior to the use of parametric statistics. Outcome data will be analysed according to a pre-planned protocol. Differences in the primary and secondary outcome measures between the two groups will be compared.

The differences between groups for the primary outcome measure of the combined incidence of the four common lower limb injuries (medial tibial stress syndrome, patellofemoral pain, Achilles tendinopathy, and plantar fasciitis/plantar heel pain) and the secondary outcome measure of the incidence of lower limb pain (overall and body region specific) during the 11 week training period will be compared using incidence rate ratios.

In regard to the other secondary outcomes, differences between groups for continuous outcome measures (severity of pain, lost training days and shoe comfort) will be analysed using independent t-tests. The time to lower limb injury and pain and drop-out will be compared using Cox proportional hazards ratios. Adherence of the shoe insole interventions will also be analysed using independent *t*-tests. The difference between groups for the outcome measure of health status (SF-12) will be compared using analysis of covariance (ANCOVA) with baseline scores and intervention group entered as independent variables [44].

95 % confidence intervals will also be provided to indicate precision of point estimates. We will also conduct hypothesis tests where appropriate, which will be considered significant if *p* < 0.05. Effect sizes will be determined using standardised mean differences (Cohen’s *d*) for continuous data.

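### Imputing recruits who leave undiagnosed from age and group alone overstates the primary injury incidence in both arms, and distorts the ratio between arms if leaving is unequal

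*Protocol article*

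**What the plan says.** Three statements in the protocol article bear on this point.

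- Outcome measures: the primary outcome is the combined incidence of four injuries, "as determined at medical appointments and by assessors at the exit interview (week 11". A positive status can therefore arise at any time in training.
- Statistical analysis: intention to treat is described as an analysis "where all randomised participants will be included in the final analyses", the endpoint is completion of 11 weeks, and "Multiple imputation will be used to replace any missing data using five iterations, with age, and group allocation as predictors". Adverse events are the only variable exempted. The primary comparison is by incidence rate ratios, with no denominator stated.
- Sample size: "306 participants (i.e. approximately 153 participants per group) are required", based on "80 % power to detect a clinically worthwhile difference of a 50 % reduction in injury in the intervention group", "a combined incidence of injury of 30 % for medial tibial stress syndrome" and the other three conditions, and "a drop-out of 20" %. On drop-out the section adds: "The drop-out rate for this trial was conservatively selected at the higher end of previous trials". No split by arm is given.

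**The concern.** A recruit diagnosed and then lost from training is a known case. A recruit who leaves without a diagnosis has not been followed to the endpoint and has no exit examination. Among leavers, then, only those undiagnosed so far can have a missing outcome, so whether the outcome is missing depends on the outcome itself.

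An imputation model with age and group cannot represent this. Within an arm it fills the gaps from completers plus every known case, including cases who later left, while the undiagnosed leavers who would balance those cases are the ones being imputed. It also assigns a full 11-week risk to people already seen to be undiagnosed for part of that time. More imputed sets would not help, nor would more baseline predictors, because neither brings in the time already served.

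At stake are the absolute incidences the trial will report and, if the arms lose recruits at different rates, the primary ratio.

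**Working it through.** **The plan's own figure.** With 30 % v 15 %, two-sided 5 % alpha, 80 % power and pooled variance, n per arm = [1.960·√(2·0.225·0.775) + 0.842·√(0.3·0.7 + 0.15·0.85)]² / 0.15² = 120.5, so 121. Then 121/0.8 = 151.25, so 152 per arm or 304 in total, against 306 stated. The sample size is not in error.

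**Inputs.** From the Sample size section: 11-week risk p of 0.30 (flat insole) and 0.15 (orthosis), and a share leaving d of 0.20. Assumed: constant injury hazard λ = −ln(1 − p); leaving times uniform over the 11 weeks and independent of injury; a share q of injuries diagnosed at a medical appointment at onset, with the rest found only at the exit interview. The documents do not give q.

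**Formulas, per arm.**
- Chance that a leaver's injury starts before departure: m = 1 − p/λ. This is 1 − 0.30/0.3567 = 0.1589 and 1 − 0.15/0.1625 = 0.0770.
- Known cases: C = (1 − d)p + d·q·m.
- Missing: L = d(1 − q·m).
- Incidence after imputation within arm: C/(1 − L).
- True risk of the missing recruits: (p − C)/L.

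**Equal leaving, 20/20, q = 1.**
- Flat insole: C = 0.24 + 0.2·0.1589 = 0.2718; L = 0.2·0.8411 = 0.1682; imputed 0.2718/0.8318 = 32.7 %. The missing recruits' true risk is 0.0282/0.1682 = 16.8 %.
- Orthosis: C = 0.12 + 0.2·0.0770 = 0.1354; L = 0.1846; imputed 0.1354/0.8154 = 16.6 %. The missing recruits' true risk is 0.0146/0.1846 = 7.9 %.
- Ratio: 0.1661/0.3267 = 0.508 against 0.500. With 30 % in both arms it is exactly 1.00.

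The missing recruits are imputed at about twice their true risk. With exponential leaving times the incidences are 32.6 % and 16.5 %. Varying the timing of injury and leaving gives 31.0–34.0 % and 15.6–17.5 %, with ratios of 0.503–0.514. In simulations with 153 per arm and five imputations, type I error was 4.5–4.9 % and power 81–82 %.

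**Unequal leaving, q = 1** (flat insole/orthosis; the splits are assumptions).

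| Split | Ratio, 30 % v 15 % | Ratio, no effect | Simulated type I error |
|---|---|---|---|
| 15/25 | 0.1713/0.3191 = 0.54 | 0.3352/0.3191 = 1.05 | 5.1–5.9 % |
| 10/30 | 0.1772/0.3121 = 0.57 | 0.3446/0.3121 = 1.10 | 8.1–8.7 % |

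Reversing the splits moves the ratio the other way. With exponential leaving times it is 0.483 at 25/15 and 0.459 at 30/10.

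**Share found only at exit.** At 20/20 and q = 0.5, the imputed incidences are 0.2559/0.8159 = 31.4 % and 0.1277/0.8077 = 15.8 %. At 10/30 with no effect, the imputed ratio is 1.10, 1.06, 1.03 and 1.00 for q = 1, 0.5, 0.25 and 0. The bias vanishes when every case is found only at exit.

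**A constant-rate person-time ratio under the same conditions.** At q = 0, 10/30 and no effect, with exit cases dated to exit, leavers average half the period. The rates are 0.70·0.30/(0.70 + 0.15) = 0.2471 and 0.90·0.30/(0.90 + 0.05) = 0.2842, a ratio of 0.87. At q = 0.5 it is 0.94. This error favours the arm with more leavers.

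**Kaplan-Meier under the same model.** Leavers are censored at departure and exit cases dated to exit. The limiting 11-week incidences are 30 % and 15 % at q = 1, 0.5 and 0.

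**The case against.** The strongest objection is that the coding is inferred. The article never says that an undiagnosed leaver is missing. Injury data are cross-checked against Defence medical records (Session 3), so such a recruit could be coded a non-case or censored, and an incidence rate ratio may already imply person-time. This stands as a limit on certainty. However, the article does fix a rule for any missing data with a single exception, and the primary outcome is not that exception. If another coding is meant, the sentence as written does not express it.

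A reader might infer that the primary ratio is biased whatever happens. The documents do not support that. Their only drop-out figure is 20 % overall, and with equal leaving the ratio, type I error and power are essentially as planned. Every material distortion of the ratio rests on assumed splits. The Discussion's 9 % v 37 % orthotic-related drop-out compares foam with semi-rigid plastic, whereas both arms here use the same foam, and uncomfortable insoles are adjusted at Session 2 in both arms. Unequal leaving is possible because the insoles differ in geometry, but it is not documented.

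A reader might also compare simulated power for imputation (74–75 % at 15/25 and 63 % at 10/30) with about 85 % for a person-time ratio and call the gap a loss from imputation. Part of it is a change of estimand: under constant hazards the rate ratio is ln(0.85)/ln(0.70) = 0.456, not 0.50. The person-time result also relies on every injury being diagnosed at onset.

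**Conclusion.** The concern holds in a limited form. On the natural reading, the rule overstates combined incidence in both arms even when leaving is equal and unrelated to injury. At 20 % leaving the excess is up to about 2.7 points (32.7 % v 30 %) and 1.6 points (16.6 % v 15 %) with uniform leaving and all injuries diagnosed at medical appointments. It is somewhat more or less under other timings, and falls towards zero as more cases are found only at exit.

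The ratio is nearly unaffected by equal leaving. It moves against the arm that loses more recruits when leaving is unequal, with a null ratio of up to 1.05 at 15/25 and 1.10 at 10/30. These sizes rest on assumed splits, on leaving being independent of injury, and on undiagnosed leavers being coded missing.

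**What to change.** In Statistical analysis, exempt the primary outcome from the age-and-group imputation and state how leavers are handled:

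- Follow each recruit from insole fitting to the first diagnosis of any of the four injuries, departure from training (censored) or the exit interview, whichever comes first.
- Date cases first found at the exit interview to that interview.
- Compare arms with a method that conditions on being still in training and undiagnosed: the ratio of Kaplan-Meier 11-week incidences, which matches the stated outcome most directly, or the Cox model already planned for time to injury, with a stated method for the ties at exit. Alternatively, impute each leaver only from same-arm recruits still undiagnosed at that departure time.
- Do not rely on a constant-rate Poisson person-time ratio alone. Leavers add time at risk with no chance of exit detection, which favours the arm with more leavers.
- Keep the age-and-group imputation as a sensitivity analysis, and report leaving by arm.

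The cost is a few sentences. Navy administration and medical records are already named as sources for drop-out and injury timing, so no new data source is needed. The downside is the assumption that departure is unrelated to injury risk within arm.

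### The primary outcome is sized as two proportions but compared by incidence rate ratios with no stated numerator, denominator or variance; under the standard Poisson variance the claimed 80% power can fall to about 72%

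*Protocol article*

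**What the plan says.** In the protocol article, the Sample size section states that "306 participants (i.e. approximately 153 participants per group") "are required to provide 80 % power" at a 5% alpha. The inputs are "a combined incidence of injury of 30" per cent, "a 50 % reduction in injury in the intervention group", and "a drop-out of 20" per cent.

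The Outcome measures section defines the primary outcome as the combined incidence of four named injuries, "as determined at medical appointments and by assessors at the exit interview (week 11"). Time to injury, in days, is a separate secondary outcome.

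The Statistical analysis section says that this outcome, and the incidence of lower limb pain overall and by body region, "during the 11 week training period will be compared using incidence rate ratios". Time to injury is assigned to Cox regression. All randomised participants are analysed, with missing data multiply imputed from age and group. Neither section says whether the numerator is recruits or injuries, whether the denominator is persons or person-time, or how the variance is obtained.

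**The concern.** The sample size treats the outcome as yes or no per recruit. An incidence rate ratio is a measure for event counts over time at risk, and its usual standard error is a Poisson one. Applied to a yes/no outcome over a common fixed period, that standard error leaves out the (1 − p) factor and is too large, so some of the planned power is lost. Applied to a count of injuries, where one recruit may contribute several diagnoses or both legs, it can be too small because injuries cluster within recruits.

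The text therefore allows several primary analyses that give different intervals and p-values from the same data. If the choice is left until the data are seen, the primary result could depend on it. The same rule governs pain incidence, where p may be larger and the missing factor matters more.

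**Working it through.** **Inputs.** From the Sample size section: 30% v 15%, alpha 0.05, power 80%, drop-out 20%, 153 per arm. Assumptions: a two-sided test (sidedness is not stated), and exponential injury times for the person-time reading.

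**1. Reproduce 306.** Two proportions, pooled variance under the null, mean proportion 0.225:

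n = [1.96·√(2·0.225·0.775) + 0.8416·√(0.30·0.70 + 0.15·0.85)]² / 0.15² = 120.5, so 121 per arm.

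Allowing for drop-out: 121/0.8 gives 152 per arm (304 in total), and 122/0.8 = 152.5 gives 153 per arm, which is 306. A Poisson rate ratio on the same inputs needs (1.96 + 0.8416)²·(1/0.30 + 1/0.15)/(ln 2)² = 163.4. That is 164 per arm, or 410 in total after drop-out. The stated figure is a two-proportion calculation.

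**2. Standard error of the log ratio at 122 per arm.** Expected injured recruits: 36.6 and 18.3.
- Poisson: √(1/36.6 + 1/18.3) = 0.286
- Binomial: √(0.70/36.6 + 0.85/18.3) = 0.256
- Ratio: 0.286/0.256 = 1.118, so 12% too wide

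Normal-approximation power, Φ(ln 2/SE − 1.96), is 67.8% for Poisson and 77.2% for binomial.

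**3. Power and type I error by reading.** The first three rows are exact enumeration over binomial counts. The last is simulated. Type I error is at 30% in both arms, 122 per arm.

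| Reading | Power, 122 per arm | Power, 153 per arm | Type I error |
|---|---|---|---|
| Two-proportion test | 81.3% | 89.0% | 5.0% |
| Rate ratio, one event per recruit, equal time, Poisson variance | 72.0% | 82.5% | 1.8% |
| Risk ratio, binomial variance | 79.8% | 88.5% | 4.7% |
| Rate ratio, person-time to first injury | 80.4% | 89.0% | 4.7% |

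In the second row, 95% intervals cover about 97–98%. The last row also estimates a different quantity: risks of 15% and 30% correspond to a rate ratio of ln(0.85)/ln(0.70) = 0.456, not 0.5.

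**4. If repeat injuries are counted.** Let p be the proportion injured and s the share of injured recruits with a second counted injury. Variance divided by mean is (1 + 3s)/(1 + s) − p(1 + s). The article gives no s. Assuming 0.3 to 0.8 at p = 0.30, the ratio runs from 1.07 to 1.35, and the Poisson standard error is 3% to 14% too narrow. At s = 0 the ratio is 0.70, so the direction of the error depends on s.

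**5. Any lower limb pain.** With equal risk p in both arms, the Poisson standard error is too wide by a factor 1/√(1 − p): 1.20 at 30% and 1.58 at 60%. The article gives no pain rate, so these powers at 122 per arm (same enumeration, 15-point difference) are illustrations only:

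| Assumed rates | Poisson variance | Two-proportion test |
|---|---|---|
| 40% v 25% | 54% | 71% |
| 50% v 35% | 41% | 66% |
| 60% v 45% | 30% | 64% |
| 70% v 55% | 21% | 69% |

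**The case against.** The strongest reply is that the article does not specify the faulty analysis. It names an effect measure and nothing more, and a Poisson model with robust standard errors yields a ratio that could fairly be reported under that name. Choice of variance is commonly left to a fuller document, which is not shown here, and the article refers to an analysis protocol planned in advance. This stands as far as it goes: a reader might infer that 80% power is not delivered and that the intervals are wrong, but the text does not support either as a flat statement. Both need the Poisson variance, one event per recruit and equal follow-up, none of which is stated.

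Three further points stand in part.
- The person-count error is conservative. It costs power but does not inflate false positives.
- The 72% assumes that the planned 20% drop-out yields no outcome data. With all 153 per arm, power is 82.5%. Imputation from age and group adds little information on injury, so the likely figure lies between the two.
- Person-time is not ruled out. Diaries date pain to the week, medical appointments supply dated diagnoses, and time to injury is collected. Against this, the diaries give no diagnosis, an injury first diagnosed at the exit interview has no diagnosis-specific onset date, and the article gives time to injury to a separate Cox analysis.

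What the objection does not remove is the mismatch itself. The article does state an effect measure for its primary outcome, it is not the measure the trial was sized on, and whether recruits or injuries are counted is left open.

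**Conclusion.** The point holds as a mismatch and an under-defined primary analysis, and should be fixed. Under the standard Poisson variance on one event per recruit with equal follow-up, the plan gives up about 9 points of power at 122 per arm (72% against 81%) and about 6.5 at 153 (82.5% against 89%), with a type I error of 1.8%. Under a robust or binomial variance, or person-time to first injury, about 80% is kept. If repeat injuries are counted, intervals could instead be too narrow. The article cannot size that, because the share of recruits with more than one injury is unknown.

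A reader might also conclude that the pain comparison is close to untestable. That goes too far: it is a secondary outcome with no stated power claim, and its loss rests on assumed pain rates and on the same unstated variance.

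**What to change.** Replace the rate-ratio sentence in the Statistical analysis section with a per-participant definition and one named model:
- **Primary outcome:** the participant has at least one of the four injuries during basic training, yes or no.
- **Primary estimate:** risk ratio and risk difference with 95% intervals, from a log-binomial model or a Poisson model with robust standard errors. Choose one now as primary. Include sex, because randomisation is stratified by it (Design section); this accompanies the fix and is not part of the defect.
- **Pain incidence, overall and by region:** the same model.
- **Injury counts or rates, if reported:** label them supportive, state the denominator, and use a variance robust to clustering within the participant.

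The sample size need not change, since the risk ratio with binomial variance has 79.8% power at 122 per arm. The cost is a sentence or two and a few lines of code, with no new data. The change should be dated before the outcome data are examined by group.

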### Participants

Participants will be naval recruits from the Australian Defence Force (ADF). The minimum age of entry for naval recruits is 17 years, with the maximum age being generally three to six years before the compulsory retirement age of ADF members (60 years) [19]. Prior to undertaking basic training, naval recruits must pass a pre-entry medical and fitness test [19]. Fitness requirements include a minimum of 20 sit-ups and a multistage 20 m shuttle run test [20] score of 6.1. The multistage 20 m shuttle run test involves running between two points that are 20 m apart and doing so within a series of pre-recorded audible beeps, with time between beeps decreasing as the test proceeds [20]. Achieving a shuttle run score of 6.1 equates to 43 shuttles or a total of 860 m in 5 min and 15 s. In addition, female and male recruits are required to perform a minimum of 6 and 15 push-ups, respectively. The maximum allowable body mass index (BMI) is 32.9 kg/m^2^; and recruits with a BMI less than 18.5 kg/m^2^ may be deemed temporary unfit by medical staff, with this decision determined in consideration of the recruit’s general and medical fitness.

All naval recruits undertaking 11 weeks of basic training at HMAS Cerberus will be invited to participate in the trial. Consecutive cohorts of recruits will be invited to participate until the pre-specified sample size (see below) is achieved. Participants will be excluded if they use foot orthoses or have a lower limb injury (causing pain of least 30 mm on a 100 mm visual analogue scale when at worst [21, 22]) at the time of recruitment. All recruits will be provided information about the study at the commencement of their 11 week training programme. Recruits interested in participating in the study will be invited to attend an initial appointment within their first week of training (session 1). Figure 1 outlines the flow of participants through the trial.

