#### Session 1 (baseline)

An initial assessment will be performed to determine the eligibility of participants. Injury history, general demographic data, physical assessments and anthropometric measures will be collected. This will include participants’ age, sex, waist and hip circumference, height and weight, foot posture [27], ankle joint dorsiflexion [28, 29], and a rating of lumbopelvic stability [30]. General health status will be determined using the Short-Form-12 Version 2 questionnaire [31] and physical activity (domestic, travel, work and recreation) in the previous four weeks will be measured using the Recent Physical Activity Questionnaire (RPAQ) [32]. Participants will also undergo a brief physical examination to determine if the clinical features used for the diagnosis of the four most expected lower limb injuries (Table 1) are present. Fitness information (e.g. multistage 20 m shuttle run test results) collected by Defence during the initial weeks of basic training will also be obtained for each participant.

**Table 1 Tab1:** Clinical features used for the diagnosis of the four most expected lower limb injuries

Injury	Clinical features
Medial tibial stress syndrome	Diffuse pain or oedema along the posteromedial border of the tibia;
	Pain spread over a minimum of 5 cm;
	Pain occurs with activity and lasts for at least a few hours post activity;
	Diffuse discomfort produced with palpation along the posteromedial border of the tibia, with discomfort confined to this region; and
	No history of paraesthesia.
Patellofemoral pain	Insidious onset of peripatellar or retropatellar knee pain;
	Pain on patellofemoral joint compression or resisted isometric quadriceps contraction at 30 degrees of knee flexion; and
	Peripatellar or retropatellar knee pain being provoked by at least two of the following activities: running, hopping, walking, marching, squatting, stair negotiation, prolonged sitting, or kneeling.
Achilles tendinopathy (midportion)	Insidious onset of pain located within 2 to 7 cm proximal to the insertion on the calcaneus; and
	Pain is reproducible with palpation of the Achilles tendon within 2 to 7 cm proximal to the insertion on the calcaneus; and
	Pain most noticeable after an extended period of rest and aggravated with activity.
Plantar fasciitis/plantar heel pain	Presence of pain in the plantar heel or medial arch;
	Pain is worse after rest but eases with mild activity;

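### The primary rate ratio and the Cox models name no baseline covariates, although injury history, age and sex are known before allocation: a modest, nearly free gain in precision, not an error

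*Protocol article*

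**What the plan says.** All references are to the protocol article.

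- **Statistical analysis, incidence.** The primary outcome (combined incidence of the four injuries) and the incidence of lower limb pain "during the 11 week training period will be compared using incidence rate ratios". No covariate is named.
- **Statistical analysis, other outcomes.** Times to injury, pain and drop-out are compared by Cox hazard ratios, again with no covariate named. Pain severity, lost training days and shoe comfort go to independent t-tests. The SF-12 alone gets an analysis of covariance on its baseline score.
- **Statistical analysis, missing data.** Multiple imputation is to be done "with age, and group allocation as predictors".
- **Session 1 (baseline).** "Injury history, general demographic data, physical assessments and anthropometric measures will be collected"; the list that follows includes age and sex. The same section places allocation after all baseline measures have been taken.
- **Design.** Randomisation is stratified by sex. Sex appears in no stated analysis.
- **Sample size.** The target is "306 participants (i.e. approximately 153 participants per group", for "80 % power to detect a clinically worthwhile difference of a 50 % reduction in injury in the intervention group".

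**The concern.** The plan adjusts for baseline where the outcome is a questionnaire score, but names no adjustment for the outcome on which the trial will be judged. Previous lower limb injury is a natural candidate predictor of a new overuse injury, and it is on file before allocation. Sex shaped the randomisation, and if it is prognostic, leaving it out of the analysis makes the standard error somewhat too large.

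The primary comparison is sized for one large effect, a halving of risk, at just over 80% power. A pre-specified adjustment would narrow the confidence interval a little and deal with chance imbalance in injury history without recruiting anyone. If it is not fixed in advance, an adjusted result presented later will look chosen after the fact.

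**Working it through.** **1. Reproduce the plan's own figure.** Inputs from Sample size: "a combined incidence of injury of 30" per cent in controls, halved to 15%; alpha 5% (taken as two-sided, which the article does not state); power 80%; "a drop-out of 20" per cent. The mean proportion is (0.30 + 0.15)/2 = 0.225.

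n per arm = [1.960 × √(2 × 0.225 × 0.775) + 0.842 × √(0.30 × 0.70 + 0.15 × 0.85)]² / 0.15²
= (1.157 + 0.489)² / 0.0225 = 120.5, rounded up to 121.

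With drop-out, 121/0.8 = 151.25, rounded up to 152 per arm, or 304 in total against 306 stated. The figure reproduces. Conversely, 306 × 0.8/2 = 122.4; with 122 analysed per arm the power is 80.5%. The sample size therefore rests on a comparison without covariates and meets its target that way.

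**2. Effect of adjustment on the primary ratio.** The documents give no predictor strengths, so they are assumed: one binary baseline predictor present in 30% of recruits, with a range of risk ratios for injury. For each value, 3,000 trials were simulated with 122 per arm at 30% v 15%. Each trial was analysed by Poisson regression with robust variance, without and with the predictor.

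| Predictor risk ratio (assumed) | Variance of log ratio, adjusted/crude | Simulated power, crude to adjusted |
|---|---|---|
| 1.0 | 1.00 | 80.0% to 80.1% |
| 1.5 | 0.99 | 81.3% to 81.6% |
| 2.0 | 0.97 | 79.2% to 80.8% |
| 3.0 | 0.92 | 80.6% to 84.4% |

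The crude column should be constant. Its spread shows the simulation error, which is √(0.8 × 0.2/3000), about 0.7 points per entry.

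**3. The same gain by formula.** Power of 80.5% corresponds to a standardised effect of 1.960 + 0.860 = 2.820. Dividing by the square root of the unrounded variance ratio:

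- 0.991 (risk ratio 1.5): power 80.8%, a gain of 0.4 points.
- 0.969 (risk ratio 2): 2.820/0.984 − 1.960 = 0.904, power 81.7%, a gain of 1.2 points.
- 0.919 (risk ratio 3): 2.820/0.959 − 1.960 = 0.981, power 83.7%, a gain of 3.2 points.

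The 3.8-point gain simulated at a risk ratio of 3 agrees with this within simulation error. A fair summary is 0 to 3 points.

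**4. In analysed recruits.** 244/0.969 − 244 is about 8, and 244/0.919 − 244 is about 22. These are equivalents in analysed participants, out of 244.

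**5. Is there room for the covariates?** Expected injuries under the design assumptions are 122 × 0.30 + 122 × 0.15 = 36.6 + 18.3, about 55. That is enough for group plus three covariates.

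**6. Does the imputation model match?** It holds age and group only. If injury history and sex enter the outcome model but not the imputation model, outcomes imputed for the assumed 20% drop-out would carry no direct link to them. Their association with injury would be diluted and part of the gain lost.

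**The case against.** An unadjusted comparison in a randomised trial is valid, and this one reaches its stated power. The article does not say that the rate ratios and Cox models exclude covariates; it only names none, and a statistical analysis plan that is not shown may list them. Both points stand. If such a list exists and was fixed before unblinding, nothing further is needed. The gain is also small and depends on assumed predictor strengths. The Discussion describes recruits as a fairly homogeneous, mostly young and healthy group, so age may add little.

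Four stronger readings are tempting, and the documents do not support them.

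- **That pain severity should be analysed by covariance on entry pain.** Pain at entry appears only as an exclusion, for recruits who "have a lower limb injury (causing pain of least 30 mm on a 100 mm visual analogue scale when at worst". No baseline pain score is listed in Session 1, the outcome list gives pain severity at week 11 only, and the diaries holding the pain scales are issued after allocation. The contrast with the SF-12, which has a stated baseline measurement, therefore fails.
- **That shoe comfort could be adjusted for its baseline.** That rating is taken after the allocated insoles are fitted, so it is not a pre-allocation value.
- **That the plan itself declares age to be prognostic.** Its place in the imputation model does not say so.
- **That the thin power margin shows a defect.** Reproducing 306 shows that the design meets its target without adjustment.

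For the Cox models, adjustment changes the target to a conditional hazard ratio. The benefit there is power, not a smaller standard error, and it was not quantified.

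**Conclusion.** The point holds as a modest efficiency improvement to the primary and Cox analyses, not as an error. The planned analysis is unbiased and adequately sized on its own assumptions. Adjustment would cut the variance of the primary log ratio by about 0 to 3% for a predictor risk ratio up to 2 and by about 8% at 3, or roughly 0 to 3 points of power. This rests on the design values (30% v 15%, 122 analysed per arm) and on one assumed binary predictor at 30% prevalence. The joint effect of injury history, age and sex was not estimated, because nothing in the documents supports figures for it. With a predictor unrelated to injury, essentially nothing is lost. Because the primary analysis would use only values already listed as collected, the change is worth making even at the low end of that range.

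**What to change.** In Statistical analysis, before unblinding:

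1. State the primary analysis as a regression of recruit-level injury (yes/no) on group, history of lower limb injury (yes/no), age and sex. Report the marginal ratio with a robust 95% confidence interval, and give the crude ratio alongside.
2. Use the same covariates in the Cox models, and say that the hazard ratio is then conditional on them.
3. Add history of lower limb injury and sex to the imputation model, so that it contains everything in the analysis model.
4. Leave pain severity without a baseline covariate, since no baseline pain score is listed.

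The cost is a few lines of text and slightly more model output. No new data are needed, because injury history, age and sex are all in the Session 1 list. The one practical check is that injury history was recorded in enough detail to be coded as lower limb injury yes/no.
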